#### 2.7.1. Standard Treatment Group (CEMR Group)

Submucosal injections must be administered with a solution commonly used at each institution. The injection time will be considered as the start time of the CEMR procedure.The lesion, including the surrounding non-tumor mucosa, should be strangled with a commercially available snare of any type or size, chosen at the discretion of each endoscopist. Bipolar snares can be used. However, EMR with the cap technique is not permitted. Although the following settings are recommended for high-frequency devices, adjustments may be made at each facility: Endo-Cut Q mode, effect 2, duration 1, interval 6 for the VIO 300D ERBE; Endo-cut Q, effect 2 for the VIO3. Specimen retrieval should be performed using a retrieval net, grasping forceps, or a snare at the discretion of the endoscopist. Intentional fragmentation is not allowed.

#### 2.7.2. Trial Treatment Group (UEMR Group)

After deflating the stomach and duodenum, the duodenal lumen must be filled with saline solution. The start time of saline immersion will be considered the start time of the UEMR procedure. Gel immersion is not permitted in this case.The lesion, including the surrounding non-tumor mucosa, should be snared under saline immersion using a commercially available snare of any type or size, chosen at the discretion of each endoscopist. Bipolar snares can be used. Although the following settings are recommended for high-frequency devices, adjustments may be made at each facility: Endo-Cut Q mode, effect 3, duration 2, interval 4 for VIO 300D ERBE, and Endo-Cut Q, effect 3 for VIO3. Specimen retrieval was performed in the same manner as in CEMR.

#### 2.7.3. Confirmation of Residual Lesions After EMR and Hemostasis

The ulcer bed will be carefully observed after EMR. If any residual lesion is identified, the allocated treatment will be repeated until the lesion is completely resected. For small residual lesions, additional excision using cold snare polypectomy, cold forceps polypectomy, or hot forceps polypectomy is permitted. However, intentional additional cauterization of the residual lesion using a snare or forceps is not permitted. In cases of bleeding, hemostasis will be achieved using clips or cauterization.

#### 2.7.4. Mucosal Closure of EMR Ulcer Bed

Commercially available standard clips with two arms will be used for complete mucosal closure. If closure with a standard clip is challenging, the line-with-clip method or an over-the-scope clip (OTSC) is permitted. If closure is performed using a device other than the standard clip, it is considered a failure of standard clip mucosal closure. The mucosal closure time will be calculated by subtracting the resection time from the total procedural time. Photographs will be captured after the completion of closure and before finishing the procedure.

#### 2.7.5. Rescue Treatment in Case of Incompletion of Allocated Endoscopic Resection Method

If the allocated endoscopic resection method is attempted repeatedly and is not completed within 15 min from the beginning of treatment, the endoscopist may switch to an alternative treatment method, such as CEMR, UEMR, ESD, or surgical resection at their discretion. In this case, the protocol treatment will be discontinued, and the procedure will be considered a failure to achieve completion.

### 2.8. Surveillance

Follow-up esophagogastroduodenoscopy (EGD) will be performed 12 ± 2 months after the EMR, and a biopsy will be obtained from the EMR scar. However, a biopsy may be omitted if the EMR scar is unclear during the follow-up EGD.

### 2.9. Outcomes

#### 2.9.1. Primary Endpoint (For Non-Inferiority)

The primary endpoint is the 1-year recurrence-free survival rate (1-year RFS), defined as the number of cases where no recurrence of SNADETs or death from any cause is observed within one year (12 ± 2 months) after EMR, with all treated cases as the denominator. Cases in which follow-up EGD cannot be performed because of tracking difficulties will be considered non-recurrent.

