### 2.5. Randomization

A randomization process will be conducted using a central web-based system to assign patients to either the CEMR or UEMR group in a 1:1 allocation ratio. For random allocation, a minimization method will be used, incorporating four allocation adjustment factors that may influence the treatment outcomes of EMR. Allocation concealment will be ensured using a central web-based system, through which treatment assignments will be generated only after patient registration and confirmation of eligibility. Investigators and endoscopists will not have access to the allocation sequence in advance and will be unable to predict upcoming assignments.

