### 2.10. Sample Size Calculation

The sample size is calculated based on the primary endpoint, 1-year RFS, to assess the non-inferiority of UEMR to CEMR.

Based on previous studies, the histological complete resection rate of CEMR for SNADET is reported to be 92–100% [2,14,24]. However, these reports are all retrospective studies with relatively short follow-up durations, which could result in a lower 1-year RFS. In this trial, the 1-year RFS in the standard treatment (CEMR) group is set at 97%. Additionally, the non-inferiority margin is set at 5%. This margin was defined as the maximum acceptable absolute excess risk of recurrence at 1 year. Prior studies of endoscopic resection for SNADETs reported very low recurrence rates under standard management. In this low-event-rate setting, an absolute margin is considered clinically interpretable. The prespecified margin of 5% was determined through multidisciplinary clinical consensus, balancing a small allowable increase in recurrence risk against the anticipated procedural advantages of UEMR.

Although the significance level of the trial is typically one-sided at 0.025 [25], the probability of decision-making error in the population with tumors at 0.05 (1 out of 20) is not considered unreasonably high according to clinical trial principles. Considering that a one-sided significance level of 0.05 was accepted in previous studies on rare diseases [12], a one-sided significance level of 0.05 is set for this study. This significance level was selected to maintain statistical feasibility in a rare disease setting with an expected extremely low event rate.

Based on these considerations, assuming a 1-year RFS of 97% for CEMR and expecting UEMR to perform equivalently, with a one-sided α error of 0.05, a non-inferiority margin of 5%, and ensuring 80% statistical power, the required sample size was calculated to be 288 cases for conducting a non-inferiority test. Considering ineligible cases and an approximately 10% dropout rate, the target enrollment number was set at 320 cases.

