#### 2.13.1. Analysis of Efficacy

The analysis of efficacy will be based on the FAS as the primary analysis population. A similar analysis will be conducted separately for the PPS. Subgroup analysis will also be performed according to preoperative biopsy status (present vs. absent), tumor length (<10 mm vs. ≥10 mm), and lesion location (bulb vs. other portions), which are allocation adjustment factors. Furthermore, an analysis of cases of untraceability (missing values) will be conducted, considering the inability to perform follow-up EGD.

Analysis of primary endpoint

The 1-year RFS, the primary endpoint, will be aggregated for each group, and the intergroup difference and the 95% confidence intervals (CI) will be calculated. The null and alternative hypotheses for the non-inferiority test are as follows:

Null hypothesis: 1-year RFS of UEMR, P1 + Δ ≤ 1-year RFS of CEMR, P2 (UEMR is inferior to CEMR by more than Δ)

Alternative hypothesis: 1-year RFS of UEMR, P1 + Δ > 1-year RFS of CEMR, P2 (UEMR is not inferior to CEMR by more than Δ)

If the null hypothesis is rejected at a one-sided 5% significance level in the non-inferiority test, we will conclude that UEMR is not inferior to CEMR. If non-inferiority in the 1-year RFS is demonstrated in the primary analysis, a test for superiority will be conducted.

2.Analysis of Secondary Endpoints
a.*En bloc* resection rate, histological complete resection rate, technical success rate, complete mucosal closure rate, and complete mucosal closure rate with standard clips: The rates for the CEMR and UEMR groups, the point estimate of the intergroup differences, and the 95% CI will be calculated.b.Total procedural, resection, and mucosal closure times: Summary statistics will be computed for both groups. The Wilcoxon rank-sum test will be used.c.One-year duodenum preservation survival rate: The rates for the CEMR and UEMR groups, the point estimate of the intergroup difference, and the 95% CI will be calculated.d.Device cost: Summary statistics will be computed for each group, and the Wilcoxon rank-sum test will be used for comparison.

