#### 2.13.3. Exploratory Analysis

An analysis considering the untraceable cases (missing values) will be conducted. If follow-up EGD cannot be performed, the events of the 1-year RFS cannot be observed, potentially affecting the primary endpoint. Therefore, sensitivity analysis considering missing values will be conducted for the primary endpoint. Missing cases in both groups will be randomly imputed to match the proportion of the presence or absence of recurrence or all-cause mortality in the population, excluding cases in which follow-up EGD was not performed from the FAS. The 1-year RFS will be aggregated for each group, intergroup differences will be calculated, and the 95% CI for both groups will be determined using the bootstrap method. Additionally, the 1-year RFS will be calculated for the FAS population, excluding cases where follow-up EGD is not performed, with SNADET recurrence or any deaths considered. Intergroup comparisons will be conducted using the same method described above to confirm that the results remain unchanged.

Moreover, post hoc analysis using multivariate analysis may be conducted to adjust for confounding factors, detect interactions, and explore prognostic factors and predictive markers.

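### The primary endpoint scores treated patients with no follow-up endoscopy as non-recurrent, which raises the false non-inferiority rate when loss is similar in both arms or heavier in the UEMR arm

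*Protocol article*

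**What the plan says.** All references are to the protocol article.

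- Section 2.8 schedules one follow-up EGD, 12 ± 2 months after resection.
- Section 2.9.1 defines 1-year RFS as freedom from recurrence and from death of any cause, "with all treated cases as the denominator". It then adds: "Cases in which follow-up EGD cannot be performed because of tracking difficulties will be considered non-recurrent".
- Section 2.13 lists the exclusions from the full analysis set (FAS). A missing EGD is not among them.
- Section 2.13.1 makes the FAS the primary population and tests "Null hypothesis: 1-year RFS of UEMR, P1 + Δ ≤ 1-year RFS of CEMR, P2" at a one-sided 5% level. The claim of non-inferiority rests on that test alone.
- Section 2.13.3, under exploratory analysis, acknowledges: "If follow-up EGD cannot be performed, the events of the 1-year RFS cannot be observed, potentially affecting the primary endpoint". It plans a random imputation at the rates seen in patients with an EGD, with bootstrap intervals, and an analysis that leaves out patients without an EGD.
- Section 3 (Discussion) promises sensitivity analyses with stricter margins.

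The document gives no reason for scoring these patients as successes.

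**The concern.** A patient who never returns for the endoscopy provides no evidence about recurrence. The rule nevertheless enters that patient into the confirmatory test as a success. Adding successes to both arms pulls the two rates together. In a superiority trial that would usually be conservative. In a non-inferiority trial it usually works in favour of the new technique.

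The Background makes the point relevant: it notes that histologically complete resection is reported as lower with UEMR and may be linked to local recurrence. That is the kind of difference the rule would partly hide. The tolerance for error is also already wide, because section 2.10 relaxes the one-sided level from the usual 0.025 to 0.05.

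**Working it through.** **Inputs from the document.** CEMR RFS 97%, margin 5 points, one-sided α 0.05 and power 80% (section 2.10); allocation "in a 1:1 allocation ratio" (section 2.5); 288 required and 320 enrolled (section 2.10). The UEMR rate at the null boundary is 97 − 5 = 92%, so the true event rates there are 3% (CEMR) and 8% (UEMR).

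**Assumptions.** The document does not give the share of treated patients without an EGD, so a range of 0 to 20% is shown. Every missing EGD is taken to fall under the rule. Loss is unrelated to outcome unless stated otherwise. All 160 per arm are treated. No test statistic is named, so both the Farrington-Manning score test and the unpooled Wald test were enumerated exactly.

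**The plan's own figure.** n per arm = (1.645 + 0.842)² × 2 × 0.97 × 0.03 / 0.05² ≈ 144, so 288 in total; 288 / 0.90 = 320. Both reproduce.

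**Effect on the difference.** If a fraction m of an arm is scored as success, its event rate becomes (1−m) times the true rate. With equal loss, the apparent deficit is 8(1−m) − 3(1−m) = 5(1−m) points, and a 5-point margin on the scored scale corresponds to 5/(1−m) points in truth.

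**Error at the null boundary, 160 per arm:**

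| Loss UEMR / CEMR | Apparent deficit (points) | Effective margin (points) | Score | Wald |
|---|---|---|---|---|
| 0% / 0% | 5.00 | 5.00 | 4.6% | 6.1% |
| 5% / 5% | 4.75 | 5.26 | 5.6% | 7.4% |
| 10% / 10% | 4.50 | 5.56 | 6.9% | 9.1% |
| 20% / 20% | 4.00 | 6.25 | 10.3% | 13.8% |
| 15% / 5% | 8×0.85 − 3×0.95 = 3.95 | – | 10.3% | 13.3% |
| 5% / 15% | 8×0.95 − 3×0.85 = 5.05 | – | 4.4% | 6.1% |

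**When the deficit shrinks.** With unequal loss the apparent deficit is below 5 points whenever 8 × (UEMR loss) exceeds 3 × (CEMR loss). Dilution therefore stops only once CEMR loss reaches 8/3 ≈ 2.7 times UEMR loss.

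**Is it the rule or the smaller sample?** Leaving out 10% at random (144 per arm) keeps the 5-point deficit and gives 4.6% (score) or 6.2% (Wald). The inflation comes from the rule.

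**Informative loss.** If recurrence is twice as common among the missing, with 10% lost per arm, the apparent deficit is 5 × (1 − 0.10×2) = 4.0 points and the error is 10.3% (score) or 13.8% (Wald).

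**Power.** At 97% in both arms, 10% loss per arm raises apparent power from 77.4% to 80.2% (score) or from 83.9% to 87.0% (Wald). Under this rule, poorer follow-up makes the trial easier to pass.

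**The case against.** Several points on the other side have force.

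- **The bias does not always favour UEMR.** A reader might infer that it does. The table shows no inflation with 5% loss in UEMR and 15% in CEMR, and if UEMR were truly better the rule would shrink its advantage. Nor does the document give grounds to expect heavier loss in UEMR: under section 2.6 patients in both arms know their allocation. This limits the claim to similar loss or heavier UEMR loss.
- **The 10% is not a stated missing-EGD rate.** Section 2.10 reads: "Considering ineligible cases and an approximately 10% dropout rate, the target enrollment number was set at 320 cases". The allowance covers ineligible patients too, and section 2.13 removes those from the FAS, along with patients with no data after randomization or no EMR. True loss to EGD may be lower; at 5% per arm the score-test error is 5.6%.
- **The sample size does not conflict with the rule.** It is tempting to say that enrolling 320 to keep 288 contradicts retaining dropouts as successes. The FAS exclusions can account for the gap, so no contradiction is established.
- **Part of the Wald figure belongs to the test.** It stands at 6.1% with nothing missing. The increase attributable to the rule is the difference from that baseline.
- **Unknown deaths are not shown to be a problem.** Observed deaths count as events, and the one-year duodenum preservation endpoint (section 2.9.2, item 10) needs survival status.
- **Safeguards exist.** The analyses in section 2.13.3, announced also in 2.13.1, and the stricter margins in section 3 would help reveal a result that depends on the rule. With equal 10% loss, a 4.5-point margin would roughly offset the dilution. A reader might infer that the trial could pass on missing data unnoticed; these analyses make that too strong. None of them alters the decision rule in section 2.13.1, however, and the two in section 2.13.3 both assume that missing patients resemble observed ones.

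**Conclusion.** The concern stands in bounded form. A stated rule in the primary endpoint treats an unobservable outcome as a success, and the confirmatory test depends on it. With similar loss in both arms, or heavier loss in UEMR, a true UEMR deficit is diluted and the chance of wrongly declaring non-inferiority rises. At 10% loss per arm the error is about 1.5 times its no-loss value under either test (6.9/4.6 and 9.1/6.1); at 5% the rise is about 1 point.

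These sizes rest on true rates of 97% and 92%, 160 treated per arm, loss unrelated to outcome, and loss rates that the document does not supply. The sample sizes of 288 and 320 are correct and are not in question.

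**What to change.** By amendment before the final analysis:

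1. Delete the non-recurrent rule from section 2.9.1 and adapt the denominator to match.
2. Name one primary analysis: observed outcomes in the FAS. Every documented recurrence or death is an event, whether or not the 12-month EGD took place. An EGD without recurrence is a non-event. Patients with neither are missing and are excluded.
3. State the death rule explicitly. Read literally, the second analysis in section 2.13.3 could drop patients who die before their EGD, so it cannot be promoted unchanged.
4. Keep the present rule and the random imputation of section 2.13.3 as sensitivity analyses.
5. Add a tipping-point analysis that includes assumptions unfavourable to UEMR, because the observed-outcome analysis still assumes that missing patients resemble observed ones.

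Scoring every missing patient as an event is not a good substitute. At 10% loss per arm the apparent deficit is still 4.5 points, the error is 6.4% (score) or 6.7% (Wald), and power falls to about 38–39%.

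**Cost.** No new data are needed. The interval becomes slightly wider, which enrolment above 288 helps to absorb. The change affects the primary endpoint of an open-label trial that has been randomizing since 18 December 2023, so it needs review-board approval under section 2.14. The study is expected to end by 30 November 2027.

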#### 2.9.2. Secondary Endpoints

The secondary endpoints and their definitions are as follows:*En bloc* resection rate

The *en bloc* resection rate is defined as the proportion of cases in which complete removal of the lesion in a single piece without residual visible tumors is achieved, with the number of treated cases as the denominator. Cases in which resection is performed using methods other than the allocated EMR will be considered failures.

2.Histological complete resection rate

Resected specimens will be appropriately oriented and pinned onto a specimen board, such as a cork, before fixation in formalin. The histological complete resection rate is defined as the proportion of cases in which *en bloc* resection is achieved without histological tumor infiltration at the horizontal and vertical margins in the specimen. The number of treated patients will be the denominator.

3.Adverse events

The adverse event rate is defined as the proportion of patients with one or more expected or unexpected complications observed up to 28 days after EMR, with the treated patients as the denominator. Adverse events will be monitored and recorded as follows:

a.Intraoperative perforation

Intraoperative perforation is defined as a suspected perforation during EMR or the detection of free air on radiography or CT immediately after EMR.

b.Intraoperative bleeding

Massive intraoperative bleeding is defined as bleeding that occurs during EMR and requires interventional radiology or surgery.

c.Delayed bleeding

Delayed bleeding is defined as clinical findings of bleeding (hematemesis, melena, or a decrease in Hb by ≥2 g/dL) observed within 28 days after EMR and confirmed bleeding from the ulcer site after EMR by EGD. Gastric or duodenal blood retention and bleeding from the ulcer site after EMR observed during second-look endoscopy without the above clinical findings are not considered postoperative bleeding.

d.Delayed perforation

Delayed duodenal perforation is defined as perforation not suspected during the procedure and first recognized on the day following the completion of EMR or later.

4.Technical success rate

Technical success is considered when the lesion is completely removed using the allocated EMR method. The number of treated patients is the denominator.

5.Total procedure time

The total procedural time is calculated only for cases of successful resection (per-protocol analysis).

CEMR: Time from the start of submucosal injection to the completion of mucosal closure.

UEMR: Time from the start of saline immersion to the completion of mucosal closure.

6.Resection time

The resection time is calculated only for cases with successful resection (per-protocol analysis).

CEMR: Time from the start of submucosal injection to the completion of lesion resection.

UEMR: Time from the start of saline immersion to the completion of lesion resection.

7.Mucosal closure time

The mucosal closure time is defined as the time obtained by subtracting the resection time from the total procedural time. Closure time is calculated only for cases with successful resection.

8.Complete mucosal closure rate

The complete mucosal closure rate is defined as the proportion of cases in which complete closure is achieved among all treated cases. Complete mucosal closure is considered if the EMR ulcer bed is not visible.

9.Complete mucosal closure rate with standard clips

Complete mucosal closure rate with standard clips is defined as the proportion of patients in whom mucosal closure is completed using only standard clips with two arms without using the clip-line method or OTSC. The number of treated patients is the denominator.

10.One-year duodenum preservation survival rate

The one-year duodenal preservation survival rate is defined as the proportion of patients in whom the duodenum is preserved without undergoing any surgical resection, and those who survive for one year after EMR. Any surgical duodenal resection and cause of death are considered events. If surgical resection occurs, information on the resected specimen will also be collected.

11.Device cost

The total cost is calculated for all treated cases and includes the cost of single-use devices (snare, ESD knife, hemostatic forceps, injection needle, injection fluid, submucosal injection fluid, clips, and OTSC) used during endoscopic resection. Device costs will be calculated based on Japanese reimbursement prices for single-use devices.

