### 2.6. Blinding

Owing to the study design, blinding endoscopists is not feasible. Endoscopists will be aware of the allocated groups at the time of treatment. Patients will also be informed of their assigned groups. Pathological assessment will be performed by pathologists who are blinded to treatment allocation.

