### 2.13. Planned Statistical Analyses

In this trial, the primary analysis will be conducted for the primary endpoint, the 1-year RFS, and this will be the final analysis. The analysis will be conducted within a year from the end date of final data collection of the registered cases by an independent biostatistician separate from the research physicians. Given the short planned registration and observation periods after protocol treatment, an interim analysis aimed at early termination will not be conducted.

The full analysis set (FAS) will consist of all enrolled patients who are randomized to the study arm, excluding some patients for the following reasons: violation of the eligibility/exclusion criteria, erroneous enrollment, no available data after randomization (e.g., withdrawal of consent), and failure to undergo EMR for SNADET. Cases in which the treatment protocol is changed or discontinued will be included in the FAS. The per-protocol set (PPS), a subset of the FAS, will exclude FAS cases with the following violations: incomplete protocol treatment and other serious protocol violations (e.g., treatment for SNADET exceeding 20 mm). The safety analysis set will include patients enrolled in this study whose treatment protocol is initiated and whose clinical course is followed for up to 28 days after the EMR. Cases in which protocol treatment has not been initiated will not be included in the safety analysis set.

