## 3. Discussion

ER is widely used for the treatment of epithelial tumors of the digestive tract, and various ER methods have been reported [26,27,28]. Numerous clinical trials have demonstrated their efficacy and safety [29,30]. Although CEMR is commonly performed to ensure an adequate margin from the muscularis propria before resection, it requires a certain level of endoscopic skill and incurs additional time and costs. Furthermore, drawbacks, such as hematoma formation owing to submucosal injection and challenges in resection caused by the non-lifting of lesions, have been encountered. To address these shortcomings, UEMR, which eliminates the need for submucosal injections, has been developed [11]. Several reports indicate that UEMR can help achieve a higher *en bloc* resection rate and lower recurrence rate, and is more effective than CEMR, especially for colorectal polyps larger than 10 mm [31,32,33]. However, considering the short-term outcomes in previous reports on SNADETs, demonstrating the superiority of CEMR over UEMR in the duodenum remains challenging [15]. Given that local recurrence is the most important outcome in clinical practice, we planned an RCT to establish the non-inferiority of UEMR to CEMR in terms of the local recurrence rate. UEMR not only offers a simpler technique but also does not require specialized devices. Based on the results of the D-CURE trial, widespread adoption of UEMR for the ER of SNADETs is anticipated, along with the dissemination of UEMR techniques.

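### Resection time and total procedure time are tested only in successful resections, so slow attempts switched after 15 minutes drop out and can bias the comparison between arms

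*Protocol article*

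**What the plan says.** All references are to the protocol article.

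- **Population for the times.** Section 2.9.2 (items 5 and 6) says of total time "The total procedural time is calculated only for cases of successful resection (per-protocol analysis" and of resection time "The resection time is calculated only for cases with successful resection (per-protocol analysis".
- **Test.** Section 2.13.1 plans: "Total procedural, resection, and mucosal closure times: Summary statistics will be computed for both groups. The Wilcoxon rank-sum test will be used".
- **Switching.** Section 2.7.5 applies when the allocated method has been tried repeatedly. If it "is not completed within 15 min from the beginning of treatment, the endoscopist may switch to an alternative treatment method". In that event "the protocol treatment will be discontinued, and the procedure will be considered a failure to achieve completion".
- **Per-protocol set.** Section 2.13 says this set "will exclude FAS cases with the following violations: incomplete protocol treatment and other serious protocol violations". Changed or discontinued cases remain in the full analysis set.
- **Who decides.** Section 2.6: "Endoscopists will be aware of the allocated groups at the time of treatment".

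Section 2.9.2 defines technical success as complete removal by the allocated method, with all treated patients as the denominator. Device cost also covers all treated cases and lists the ESD knife, so rescued cases count towards cost but not towards time. No time analysis in all treated patients is described.

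**The concern.** Success with the allocated method is known only after randomisation, and the 15-minute rule ties it directly to the duration being tested. A slow attempt that is switched leaves the comparison; an equally slow attempt that is carried through stays in. The retained cases are no longer randomised groups, and which slow cases are retained depends partly on an operator who knows the arm.

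This can do harm in two ways. If operators switch more readily in one arm, that arm loses more of its upper tail and looks faster than it is. If one technique really is slower, more of its attempts pass 15 minutes, so an identical switching habit in both arms still trims the slower arm more and shrinks the difference.

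At stake is what the trial reports about speed. The Discussion says of CEMR that "it requires a certain level of endoscopic skill and incurs additional time and costs", and these two endpoints are the planned tests of the time part. No decision rule uses their p-values. The primary endpoint and the non-inferiority conclusion are untouched.

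**Working it through.** **Inputs from the protocol.** Section 2.10 gives 288 evaluable patients, 1:1. This reproduces: n per arm = (1.645 + 0.842)² × 2 × 0.97 × 0.03 / 0.05² = 143.9, so 144 per arm and 288 in total; 288 / 0.90 = 320. The switching threshold is 15 minutes and the test is the rank-sum. The protocol states no figure for the time endpoints.

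**Assumed inputs.** Two-sided 5% level; lognormal resection times with log-SD 0.7; a share p of attempts passing 15 minutes; each such attempt switched with an arm-specific probability. Switching is written CEMR/UEMR, so 80/30 means 80% and 30%. The choice of arm is arbitrary. For total time, an independent closure time is added (median 8 min, log-SD 0.6, equal in both arms).

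**Hand check, no true difference, p = 10%, switching 80/30.**
- CEMR keeps 0.90 below and 0.10 × 0.2 = 0.02 above 15 minutes, 0.92 in all. UEMR keeps 0.90 below and 0.10 × 0.7 = 0.07 above, 0.97 in all.
- P(CEMR shorter) = (0.90²/2 + 0.90 × 0.07 + 0.02 × 0.07/2) / (0.92 × 0.97) = 0.4687 / 0.8924 = 0.525.
- With 132 and 140 cases retained, SE = √(273 / (12 × 132 × 140)) = 0.0351, so z = 0.72.
- Rejection probability = P(Z > 1.96 − 0.72) + P(Z < −1.96 − 0.72) ≈ 11%.

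For resection time with no true difference, this result depends only on p and the switching rates, not on the lognormal shape.

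**Simulation, no true difference (8,000 runs per scenario), rejection rate at switching 80/30:**

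| Share past 15 min | Resection, success-only | Resection, worst rank | Resection, 15-min tie | Total, success-only | Total, worst rank |
|---|---|---|---|---|---|
| 2% | 5.0% | 4.6% | 4.7% | – | – |
| 5% | 6.2% | 4.7% | 4.6% | 5.9% | 4.5% |
| 10% | 11.1% | 4.9% | 4.8% | 9.2% | 5.1% |
| 20% | 29.7% | 6.0% | 5.0% | 22.0% | 7.7% |
| 30% | 53.7% | 10.0% | 4.8% | 41.3% | 14.5% |

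At 60/40 the success-only test of resection time rejects 5.3%, 6.0% and 8.6% (5%, 10% and 20% past 15 minutes). At equal switching it stays near 5%. At 80/30 the spurious difference in medians is 0.09, 0.27 and 0.68 min at 5%, 10% and 20%.

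**Simulation, real difference in resection time.** Medians are 7 (CEMR) and 5.7 min (UEMR), so ln(15/7)/0.7 = 1.09 and ln(15/5.7)/0.7 = 1.38, giving 14% and 8% past 15 minutes. With no switching, power is 67.6% and the difference in medians 1.30 min.

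| Switching CEMR/UEMR | Power, success-only | Power, worst rank | Power, 15-min tie | Success-only difference in medians |
|---|---|---|---|---|
| 80/30 | 27.2% | 69.9% | 67.0% | 0.77 min |
| 50/50 | 59.4% | 67.8% | 67.8% | 1.10 min |
| 100/100 | 48.1% | 67.5% | 67.5% | 0.90 min |
| 30/80 | 84.7% | 64.6% | 68.0% | 1.38 min |

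The 100/100 row involves no arm-dependent discretion, yet about 20 percentage points of power are lost.

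**The case against.** The strongest reply concerns materiality. Every input on times and switching is assumed. With no true difference, serious inflation needs both a sizeable share of attempts past 15 minutes and clearly unequal switching between equally fast arms, and the protocol documents no such gap. Section 2.7.5 requires repeated attempts first. Section 2.7.3 allows re-treatment and small-residual excision, and technical success does not require en bloc removal, so many slow cases stay in. The en bloc rates and the 24.6% non-lifting figure in section 2.5 are not switching rates. This stands: the size is unknown and may be negligible. It does not answer the power loss, which occurs even with equal switching.

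Second, unequal failure would be visible in technical success, en bloc resection and device cost. True, but that shows how many cases failed and does not correct the time test.

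Third, the duration of the procedure when it works is a legitimate and openly labelled quantity. That supports keeping it as a description. It does not make a between-arm test among selected completers a randomised comparison.

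Fourth, the remedy has flaws: worst rank mixes failure with time and is not fully immune to unequal switching, and changing two of three linked time endpoints leaves closure time on a different population. These costs are real and should be stated with the change.

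**Conclusion.** The concern holds. The protocol itself fixes a time comparison restricted to cases selected after randomisation by a rule based on elapsed time, and nothing in it supplies an all-treated alternative.

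Under the assumptions above, the effect is negligible if 2–5% of attempts pass 15 minutes. It is material at 10–20% with clearly unequal switching, where a nominal 5% test rejects 11–30% of the time for resection time and 9–22% for total time. In minutes the spurious difference is modest, below 1 min in those scenarios. With a real difference of 7 versus 5.7 min, power can fall from 68% to 48% with uniform switching, or to 27% if the slower arm is switched more. The direction is open, since the documents do not say which arm will switch more. Only the two secondary time endpoints are involved. The change should be made, but the validity of the trial's main conclusion does not depend on it.

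**What to change.** For resection time and total procedure time:

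1. Run the between-arm Wilcoxon test in all treated patients, giving every case switched from the allocated method the same worst tied rank. Report the number switched per arm.
2. Keep the success-only times as a labelled descriptive summary of speed among completers, read beside technical success.
3. For resection time, add one sensitivity analysis that ties every case not resected by the allocated method within 15 minutes, whether later switched or completed. The switching option opens only at 15 minutes, so the choice to switch or persist cannot move this result.

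Technical success, en bloc resection, the per-protocol set, mucosal closure time and the permission to switch stay as they are.

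The cost is analysis wording for two secondary endpoints, by amendment, with no new data: failure status and times are already collected. The trial is open-label and has randomised since December 2023, so the amendment should state that no between-arm time data had been tabulated. The tested quantity becomes time with failure counted as worst, and some operator influence remains, because a case switched at 16 minutes ranks below one completed at 40. The 15-minute tie removes that influence for resection time only, ignores differences beyond 15 minutes, and assumes no earlier switches.
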